### **7.1.5 Participant Selection Criteria**

#### **7.1.5.1 Inclusion Criteria**

To be eligible for the trial, a patient must meet all of the following criteria:

**7.1.5.1.1 Age:** Between 18 and 75 years old.

**7.1.5.1.2 Diagnosis:** Diagnosed with tricuspid valve disease (e.g., degenerative or functional valve pathology) requiring surgical repair.

**7.1.5.1.3 Heart Function: Preoperative New York Heart Association (NYHA)**

functional class III or lower.

**7.1.5.1.4 Consent:** Willing and able to provide written informed consent, comply with follow-up visits, and complete required postoperative evaluations.

**7.1.5.2 Exclusion Criteria**

A patient will not be eligible if they meet any of the following conditions:

**7.1.5.2.1** Contraindications for Annuloplasty Ring implantation or Previous tricuspid valve surgery.

**7.1.5.2.2** Severe Heart Conditions: NYHA class IV heart failure, Right heart failure.

**7.1.5.2.3** Researchers determine patients with increased surgical risks due to thrombus in the right atrium or right ventricle.

**7.1.5.2.4** History of heart transplant.

**7.1.5.2.5** Emergency surgery requirement.

**7.1.5.2.6** Life expectancy less than 1 year.

**7.1.5.2.7** Recent cardiac surgery, interventional procedure, or stroke within the past 3 months.

**7.1.5.2.8** Kidney failure requiring dialysis.

**7.1.5.2.9** Severe respiratory disease.

**7.1.5.2.10** Active infective endocarditis.

**7.1.5.2.11** Active systemic infection, sepsis, or unexplained fever.

**7.1.5.2.12** Active gastrointestinal bleeding, peptic ulcers, or hypercoagulability in the blood.

**7.1.5.2.13** Contraindications to anticoagulants/antiplatelet therapy.

**7.1.5.2.14** Allergies: Known hypersensitivity to nitinol, silicone, or polyester materials.

**7.1.5.2.15** Pregnancy: Currently pregnant or breastfeeding.

**7.1.5.2.16** Other Trials: Participation in another drug or device study.

**7.1.5.2.17** Miscellaneous: Any condition deemed unsuitable for enrollment by the investigator.

**7.1.5.3 Criteria and Procedures for Stopping the Trial or Trial Treatment****7.1.5.3.1 Serious Safety Concerns**

If significant safety risks are identified during the trial, immediate action will be taken to protect participants. The trial may be paused or stopped if necessary.

#### **7.1.5.3.2 Major Errors or Deviations in the Trial Protocol**

If serious mistakes or deviations in the trial plan occur, making it impossible to reliably evaluate the safety or effectiveness of the product, the trial will be discontinued.

#### **7.1.5.3.3 Sponsor's Decision to Stop the Trial**

The sponsor (the organization managing the trial) may stop the trial for reasons such as funding issues, administrative challenges, or other logistical concerns.

#### **7.1.5.3.4 Regulatory Authority Decision**

The trial will be stopped if a regulatory agency withdraws approval or orders termination. In any of these cases, the sponsor must immediately inform all participating hospitals, investigators, and ethics committees. For participants who have already received the trial treatment, the sponsor will continue to follow legal requirements and uphold responsibilities outlined in the informed consent form. Participants have the right to withdraw from the trial at any time for any reason. Researchers also have the right to withdraw participants from the trial in the event of complications, adverse events, treatment failure under standard therapy, violation of the protocol, cure, or other reasons.

Excessive participant withdrawals can compromise the reliability of the trial results. Therefore, every effort should be made to avoid unnecessary withdrawals. If a participant decides to withdraw, the investigator should make every effort to persuade them to stay and document the reasons for withdrawal in detail. Documenting Withdrawal Reasons. If a participant withdraws due to an adverse event or abnormal lab results, the investigator must record the event or abnormality in the electronic Case Report Form (eCRF). The investigator should also attempt to contact the participant (or their family) via phone, in-person visits, or other means to gather detailed information about the withdrawal. Specific Reasons for Discontinuation by the Investigator.

The investigator may also decide to discontinue a participant's involvement in the trial under the following circumstances:

**Pregnancy:** If the participant becomes pregnant during the trial.

**Protocol Violations:** If the participant fails to follow the trial procedures or requirements.

**Complications or Adverse Events (AEs):** If the participant experiences serious side

effects, abnormal lab results, or other medical conditions that could worsen by continuing the trial.

**Non-Compliance:** If the participant fails to adhere to the trial treatment or procedures.

**Adverse Events or Medical Conditions:** If continuing the trial poses a risk to the participant's health.

**Disease Progression:** If the participant's condition worsens, requiring discontinuation of the trial treatment.

**Loss to Follow-Up:** If the participant misses three scheduled follow-up visits and cannot be contacted despite repeated attempts, they will be considered lost to follow-up and withdrawn from the trial.

Severe non-compliance with study intervention;

Clinical adverse events (AE), laboratory test abnormalities or other disease conditions that would be detrimental to the subject if continued participation in the trial;

Disease progression that requires discontinuation of trial intervention;

**Non-Interview:** If a participant is unable to be interviewed during the specified visit period, the researcher or authorized investigator will make every effort to contact the participant before confirming their non-interview status; if a participant is missing three scheduled follow-ups and the researcher cannot reach them, they will be considered non-interviewed and will be deemed to have withdrawn from the trial, with the reason for withdrawal being non-interview.

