| 
Statistical Methods:
 
This trial plans to enroll 164 patients, who will be randomly assigned to either the experimental group or the control group in a 1:1 ratio, with 82 cases in each group.
 
The primary endpoint of this clinical trial is the success rate of valve repair at 6 months postoperatively, defined as no severe regurgitation and an increase in annular diameter of <math>\leq 15\%</math> based on echocardiographic evaluation. According to literature reports and clinical experience, the expected success rate of valve repair in the control group at 6 months postoperatively is 95%. Assuming that the investigational medical device can achieve comparable efficacy, the clinically accepted non-inferiority margin is set at -10%. With a one-sided significance level of 0.025 and a power of 80%, the sample size was estimated using PASS 14.0 software, indicating that 75 cases are required for each group. Considering potential dropouts during the study, the plan is to enroll 82 cases per group, totaling 164 cases.
 
The trial results will be determined based on the difference in the primary efficacy endpoint between the experimental group and the control group. If the lower limit of the 95% confidence interval for the difference in success rates between the experimental group and the control group is
 |                                                                                                                                                                                                                                                                                                                                                                                                                                                                                                                                                                                                                                                                                                                                                                                                                                                              |

greater than -10% (the predefined non-inferiority margin), the non-inferiority conclusion will be established. Otherwise, the non-inferiority conclusion will not be supported.

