## **8.2 Calculation of sample size**

### **8.2.1 Total sample size**

According to literature reports and clinical experience, it is estimated that the success rate of valve repair with a prosthetic ring in the control group 6 months post-surgery is 95%, with a non-inferiority margin of -10%. Using a one-sided test,  $\alpha=0.025$ ,  $\beta=0.2$  (power 80%), the trial group and control group are to be matched at a ratio of 1:1. Using PASS 14.0 software, it is estimated that each group will require 75 cases. Considering the risk of dislodgement during the study process, it is planned to enroll 82 cases in each group, totaling 164 cases.

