#### **8.7 Statistical methods for all data, including processing of missing, unused or erroneous data (including dropout and withdrawal) and unreasonable data**

When the main indicators are missing, the last observation value carry-over method (LOCF) is used to fill in the data. Other indicators are analyzed using the actual collected data.

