### **8.9 Selection criteria and reasons for subjects included in the analysis**

Full analysis set (full analysis set, FAS): The collection of all cases randomized to the group and who received surgical implantation devices.

Conformity set (per protocol set, PPS): A subset of the full analysis set, a data set generated by subjects who are fully compliant with the protocol, compliance including treatment received, availability of measurement of primary endpoint indicators, and no significant deviation from the protocol. PPS analysis is used for primary efficacy endpoints.

Safety Dataset (safety set, SS): All actual data that were randomly enrolled and underwent surgical implantation of devices and had post-implant safety metrics recorded. SS analysis was used for primary safety metrics.

Efficacy analysis will be performed on the full analysis set and the compliant set. All baseline demographic data analysis will be performed on the full analysis set and safety evaluation will be performed on the safety set.

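### Investigators may end trial participation for outcome-related reasons with no 6-month echo required afterwards, which can hide primary-endpoint failures from the PPS and, through LOCF, from the FAS

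*Protocol*

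**What the plan says.** **Withdrawal.** Protocol section 7.1.5.3.4 gives investigators a general power: "Researchers also have the right to withdraw participants from the trial in the event of complications, adverse events, treatment failure under standard therapy". The same sentence adds protocol violation, cure and other reasons. A list of specific reasons follows, including pregnancy, non-compliance, adverse events and worsening disease. It is then partly repeated, with the entry "Disease progression that requires discontinuation of trial intervention". The section also says that unnecessary withdrawals should be avoided, that reasons must be documented, and that the investigator should try to reach the patient. It does not ask for the 6-month echo after an investigator-initiated withdrawal, and no other section does.

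**Endpoint.** Success at 6 months means no severe regurgitation and a diameter increase of at most 15% (section 7.1.6.1). The ring is implanted on Day 0 (section 7.2.2). Echo is scheduled at discharge or 30 days and at 3, 6 and 12 months.

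**Analysis.** Section 8.7: "When the main indicators are missing, the last observation value carry-over method (LOCF) is used to fill in the data". Section 8.9 puts every randomised and implanted patient in the FAS. It makes PPS membership depend, among other things, on "availability of measurement of primary endpoint indicators", and names the PPS for the primary efficacy endpoint. Section 8.1.5 requires both sets to be analysed, using the Newcombe interval and the -10% margin.

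**The concern.** With a permanent implant there is no continuing device treatment to stop, so withdrawing a patient stops the observation. Two of the listed grounds, treatment failure and worsening disease, lie close to what the endpoint measures. Some complications do too. Surgeons implant the allocated ring and no masking of site staff is described, so the decision can be taken knowing the arm. The independent echo reading in the notes to section 7.2.8 does not help when no echo is taken.

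The two analysis sets are exposed differently. A withdrawn patient without a 6-month echo is out of the PPS. In the FAS the patient stays, and an acceptable early echo can stand in for a later failure. If failures are lost at similar rates in both arms, or more often in the test arm, the observed difference shrinks towards zero and a non-inferiority claim becomes easier. Agreement between FAS and PPS would then be weak reassurance, because the same lost echoes affect both. No analysis plan can recover a measurement that was never made, so this belongs in the protocol.

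**Working it through.** **Inputs from the protocol.** Control success 95% (section 8.2.1); test success equal to it (synopsis, statistical methods: "Assuming that the investigational medical device can achieve comparable efficacy"); margin -10 points; one-sided 0.025; power 80%; 82 enrolled per arm; expected fall-off about 10% (section 8.4).

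**Assumptions.** The share *w* of true failures withdrawn before month 6, and the share *d* of those whose last echo already showed failure. The protocol gives neither, so ranges are shown.

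**The plan's own figure.** n = (1.960 + 0.842)² × 2 × 0.95 × 0.05 / 0.10² = 74.6, rounded up to 75 per arm. This matches the protocol. Enrolment is 82.

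**Decision rule.** With Wilson limits l and u for each arm, the Newcombe lower limit is p₁ - p₂ - √[(p₁ - l₁)² + (u₂ - p₂)²]. Non-inferiority is claimed if this exceeds -0.10. The false-claim rate is evaluated at the margin: test 85%, control 95%, 82 per arm. Expected failures are 82 × 0.15 = 12.3 and 82 × 0.05 = 4.1.

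**Effect of withdrawal on the apparent success rate**
- PPS (withdrawn failures removed): p / [p + (1 - p)(1 - w)]
- FAS (last echo carried forward): p + (1 - p) × w × (1 - d)

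Example with w = 50% in both arms:
- PPS: 0.85/0.925 - 0.95/0.975 = 0.919 - 0.974 = -5.5 points.
- FAS, d = 0: 0.925 - 0.975 = -5.0 points.
- FAS, d = 0.5: 0.8875 - 0.9625 = -7.5 points.

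The true difference is -10 points in each case.

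**False non-inferiority rate, same w in both arms** (FAS by exact binomial enumeration, PPS by simulation)

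| Failures withdrawn | PPS | FAS, none documented | FAS, half documented |
|---|---|---|---|
| 0% | 2.4% | 2.4% | 2.4% |
| 20% | 5.1% | 5.9% | 3.7% |
| 30% | 7.6% | 9.4% | 4.7% |
| 50% | 17% | 23% | 7.5% |

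The third column is an upper bound for the FAS. If every withdrawn failure had been documented (d = 1), the FAS rate would stay at 2.4%.

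**Unequal withdrawal.** With 50% of failures withdrawn in the test arm only, the rate is 34% (PPS) and 43% (FAS, none documented). With 50% withdrawn in the control arm only, it is 0.5% in both sets.

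**How few patients this takes.** The 50% row means 6.15 + 2.05 = 8.2 of 164 patients, or 5%, which is inside the expected fall-off. The 20% row means about 2.5 test and 0.8 control patients.

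**Sensitivity to one patient.** With 78/82 control successes (u₂ = 0.981):
- 5 test failures: -0.0122 - √(0.0739² + 0.0297²) = -9.2%, a pass.
- 6 test failures: -0.0244 - √(0.0774² + 0.0297²) = -10.7%, not a pass.

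**The case against.** A reader might infer that failures vanish from both analysis sets. They do not. The FAS keeps every implanted patient, and severe regurgitation already seen on an earlier echo is carried forward as a failure. Someone withdrawn for treatment failure may well have such an echo. The FAS figures with no documented failures are therefore a ceiling, and with half documented the effect is much smaller. This objection stands. It leaves the PPS figures untouched.

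A reader might also infer that the rule always favours non-inferiority. It does so only when failures are withdrawn at similar rates or more often in the test arm; the control-arm-only case shows the opposite. This stands too.

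Nor does every listed reason point to failure. Cure describes a success, and pregnancy, abnormal laboratory results or bleeding are not echo findings. The power is permissive, several specific reasons carry conditions, and the text discourages unnecessary withdrawals. All true, but the general sentence naming complications and treatment failure carries no condition, and the safeguards recover the reason for withdrawal, not the outcome.

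Finally, part of the harm works through LOCF and the PPS definition, and the detail of the data sets is left to the analysis plan. Better imputation would still have to work without the 6-month echo.

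**Conclusion.** The point holds in a limited form. The protocol permits outcome-related withdrawal from observation after a one-time implant and does not require the primary measurement afterwards. The PPS is directly exposed. The FAS is exposed only where the last echo was still a success. In addition, under the definition in section 7.1.6.2.2, where diameter increase is taken from month 3, a patient withdrawn before 3 months has no diameter increase to carry forward.

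Under similar withdrawal in both arms, the false-claim rate at the margin moves from about 2.4% to 5.1–17% in the PPS. In the FAS it moves to somewhere between no change and 5.9–23%, depending on how many failures were documented first. These figures rest on assumed withdrawn shares of 20% to 50% of failures, on true rates of 85% and 95%, and on only failures being withdrawn. They show what the rule allows, not what will happen. The documents do not support saying that both sets lose failures, that the direction is fixed, or that every withdrawn patient is a likely failure.

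**What to change.** In section 7.1.5.3.4, separate stopping trial procedures from ending outcome collection. State that every implanted patient who has not withdrawn consent continues the scheduled visits where possible, including the 6-month echo, whatever the complication, adverse event, worsening, protocol deviation or non-compliance.

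In sections 7.1.6 and 8.9, state that reoperation for tricuspid regurgitation, or documented severe regurgitation leading to withdrawal before month 6, counts as a primary-endpoint failure in both the FAS and the PPS. The PPS requirement for an available measurement should not remove these patients.

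Counting every withdrawal as a failure is not proposed. At true success of 95% in both arms and 82 per arm, Newcombe power is 74%. It would fall to 55% if a further 5% of patients in each arm, withdrawn for unrelated reasons, were counted as failures.

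The investigator's discretion over clinical care is unchanged; this concerns data collection and endpoint counting only. The cost is protocol wording, site training and possibly a slightly lower observed success rate. The visits are already scheduled.

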#### **7.1.5.4 Enrollment Time**

The clinical trial is planned to be conducted at no more than 20 trial sites nationwide, with an expected enrollment period of approximately 12 months.

#### **7.1.5.5 Expected Overall Duration of the Clinical Trial and Its Rationale**

The planned duration of the clinical trial is 84 months.

Ethical approval is expected to take around 6 months. After obtaining ethical approval, completing provincial drug regulatory agency filing, and meeting other relevant policy and regulatory requirements, the trial can commence. It is planned to enroll 164 subjects within approximately 12 months after the trial starts. Clinical follow-ups will be conducted at discharge or 30 days, 3 months, 6 months, and 12 months postoperatively, recording transthoracic echocardiography (TTE), adverse events, etc. Data processing, statistical analysis, and medical summarization will be

performed after completing the 6-month follow-up, followed by registration application. A phase summary will be conducted at the 12-month postoperative mark, while long-term follow-ups and summaries will continue for up to 5 years postoperatively. Therefore, the expected overall duration of the trial is approximately 84 months.

#### **7.1.5.6 Expected Duration of Participation for Each Subject**

Each subject is expected to participate in the trial for a duration of 5 years, including preoperative screening, intraoperative heart valve annuloplasty treatment, and follow-ups at discharge or 30 days ( $\pm 7$  days), 3 months ( $\pm 15$  days), 6 months ( $\pm 30$  days), 12 months ( $\pm 30$  days), and annually from 2 to 5 years ( $\pm 30$  days) postoperatively.

#### **7.1.5.7 Required Number of Subjects for the Clinical Trial**

Based on statistical calculations, a minimum of 164 subjects will be enrolled.

### **7.1.6 Efficacy Evaluation Methods**

#### **7.1.6.1 Description of Efficacy Parameters**

Primary efficacy endpoint: The success rate of valve annuloplasty repair at 6 months postoperatively, defined as no severe regurgitation and an increase in diameter  $\leq 15\%$  (based on a comprehensive assessment of regurgitation severity and diameter increase).

Other efficacy endpoints:

**7.1.6.1.1** At discharge or 30 days postoperatively (whichever comes first), 3 months, 6 months, and 12 months:

- Degree of valve regurgitation assessed by echocardiography (evaluated according to the tricuspid regurgitation assessment index table).
- Changes in echocardiographic parameters (right atrial and ventricular size, diameter, width of the narrowest regurgitation jet, and reverse flow area).
- NYHA functional class.
- Freedom from reoperation due to tricuspid valve insufficiency.

**7.1.6.1.2** Evaluation of the trial device's performance, including needle insertion smoothness and user-friendliness of the ring holder.

**7.1.6.1.3** Technical success rate of the surgery (before leaving the operating room), defined as no intraoperative death, successful implantation of the annuloplasty ring, successful removal of the ring holder, and no emergency surgery or secondary

intervention related to the trial device.

### 7.1.6.2 Methods and Timing for Evaluating, Recording, and Analyzing Efficacy Parameters

**7.1.6.2.1** Valve annuloplasty repair success is defined as no severe regurgitation and an increase in diameter  $\leq 15\%$  (based on a comprehensive assessment of regurgitation severity and diameter increase).

Tricuspid Regurgitation Assessment Index Table

| Parameter                   | None                                     | Trace                                                        | Mild               | Moderate                                            | Severe                 |
|-----------------------------|------------------------------------------|--------------------------------------------------------------|--------------------|-----------------------------------------------------|------------------------|
| Regurgitation Jet           | No regurgitation jet in the right atrium | Regurgitation jet extends $\leq 1$ cm from the valve orifice |                    |                                                     |                        |
| Absolute Regurgitation Area |                                          |                                                              | $< 5 \text{ cm}^2$ | $5 \text{ cm}^2 \leq \text{area} < 10 \text{ cm}^2$ | $\geq 10 \text{ cm}^2$ |
| Regurgitation Area Fraction |                                          |                                                              | $< 20\%$           | $20\% \sim 33\%$                                    | $\geq 33\%$            |

Absolute regurgitation area: Measured by TTE or TEE in the standard view with the most regurgitation.

Regurgitation area fraction: Measured by TTE in the apical four-chamber view or TEE in the mid-esophageal four-chamber view, or in the standard view with the most regurgitation.

